### Management

Participants will be informed of the group to which they will be randomly assigned at the beginning of the study. Participants in each group will be systematically asked about the content of the interventions received to maintain engagement and compliance. Due to the nature of the intervention participants cannot be blinded to allocation and since therapists are required only for the FtF group, no information sharing will occur between clinicians in both groups. Furthermore, since interventions and assessments will occur at very distant places in the FtF and TR, between groups contamination will be unlikely. There will be one independent assessor (clinician external to the research team) for each of the intervention groups. All data will be recorded in unidentifiable datasheets so researchers will be able to independently analyse data without having access to information about the allocation. To identify raw data well as processed posturographic metrics and clinical outcomes measures, all electronic files will be coded and backed up every week.

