## Materials and methods

### Design

This is a double blinded (therapist and assessors), randomized, controlled trial designed following the Standard Protocol Items: Recommendations for Interventional Trials (SPIRIT), (Fig 1) [21].

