**Fig 1 pone.0268163.g001:**
[figure not shown]
Flow chart according to the standard protocol items: Recommendations for interventional trials (SPIRIT). Participants, assessments and interventions. Through the two groups of the trial.

The TR interventions does not require a therapist as in the FtF group, where therapist did not know about the participant’s involvement in the trial (therapist blinding). Assessors will not be able to identify the intervention group either. The trial adheres to the Declaration of Helsinki and the Chilean laws of rights and duties of the patient and research in humans. Ethical approval was obtained from the Ethics Committee of the University of Talca (Ref. No. 24–2018). This study was registered with the Australian and New Zealand Clinical Trials Registry (ACTRN12621000117819). Written informed consent will be obtained from parents and participants over 7 years old; verbal assent will be obtained from younger children.

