### Study setting

This study will compare the effect of low-cost virtual reality in two distinct settings. The first setting will be clinical (Telerehabilitation Technology Centre and Neurosciences in Human Movement, Universidad de Talca, Chile) and in which low-cost virtual reality will be delivered in a FtF modality (control group) with therapist interacting directly with the patient. The second setting will be a remote facility with no therapist on-site for the delivery of low-cost virtual reality through TR. The default TR setting will be at-home, however, if a participant does not have adequate access to space and/or equipment, TR will be delivered at school, or rehabilitation centre. To note, in the latter cases (school and rehabilitation centre) no therapist will be involved in the TR delivery. All assessments will be conducted at the same facility in which the therapy will be delivered.

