### Data collection

All measurements will be performed at the same time of the day, under the same conditions and by the same assessor at each time point. Posturographic (CoP) measures for both groups will be collected using an AMTI OR67 force platform (Watertown, MA, USA). The AMTI NetForce software (Watertown, MA, USA) will be used for the acquisition of moments and forces at 200Hz. Data will be recorded, coded, and stored on a personal computer. CoP variables will be calculated in Matlab R2012 (Mathworks Inc., Natick, MA, USA).

All primary and secondary posturographic measures will be assessed under 2 static and 4 dynamic conditions for 30 seconds each: (i) standing still with eyes open, (ii) standing still with eyes closed, voluntary sway in the mediolateral direction following a metronome set at (iii) 30Hz and (iv) 60Hz, and multidirectional sway while playing 2 different videogames that challenge (v) anterior-posterior postural control (snowboard) and (vi) medial-lateral postural control (pinguin). It is expected that all assessments, including clinical ones, will be completed within 30 minutes.

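### Each arm has its own assessor and is measured where it is treated, so assessor and place are confounded with arm and the assessor-blinding claim does not fit the design

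*Protocol article*

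**What the plan says.** All references are to the protocol article.

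- **Who assesses (Management):** "There will be one independent assessor (clinician external to the research team) for each of the intervention groups".
- **Where (Study setting):** "All assessments will be conducted at the same facility in which the therapy will be delivered". The face-to-face (FtF) arm is treated at the university centre. The telerehabilitation (TR) arm is treated at home by default, otherwise at a school or rehabilitation centre, with no therapist on site.
- **How far apart (Management):** "since interventions and assessments will occur at very distant places in the FtF and TR, between groups contamination will be unlikely". The distance is offered as a safeguard.
- **Blinding (Design):** the trial is called "double blinded (therapist and assessors)", and the text below Fig 1 adds "Assessors will not be able to identify the intervention group either". Management concedes that participants know their group.
- **Measurement conditions (Data collection):** measurements are to be made "under the same conditions and by the same assessor at each time point", on one named model of force platform for both groups.
- **Analysis (Data analysis):** FtF and TR are compared by t-test or Mann–Whitney U. A repeated-measures ANOVA or Friedman test is also planned. The text does not say whether the between-group test uses week-6 values or change from baseline, or whether the ANOVA has a group factor.

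**The concern.** The comparative question is whether TR does as well as FtF. If one assessor measures only FtF children at the university centre, and another measures only TR children in homes, schools or rehabilitation centres, then differences in instruction, foot placement, floor, surroundings or equipment set-up run along the same line as the treatment. A measured FtF–TR difference, or the lack of one, could then partly reflect who measured and where.

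Blinding is the second issue. The place of assessment and the identity of the assessor each reveal the arm. Readers who rely on the stated assessor blinding would give the rater-dependent outcomes (MAS, MMAS, TUG, TOLS and 6MWT) more credit than the design supports. Because the trial hopes to show that TR is as effective as FtF, an offset that hides a real difference matters as much as one that creates a false one.

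**Working it through.** **1. The statements side by side**

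| Feature | FtF | TR |
|---|---|---|
| Assessor (Management) | FtF assessor | TR assessor |
| Place (Study setting) | University centre | Home, school or rehabilitation centre |
| Therapist present during therapy (Study setting) | Yes | No |

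The assessor indicator and the arm indicator are the same column of the design matrix. A model of post-treatment values cannot estimate both, whatever the sample size. Place is nested in arm: TR may use several places, but Management puts them far from the FtF place. Stratifying randomisation by site (Allocation) does not help, because the place of assessment follows from the allocated arm.

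**2. Blinding.** To be blind, an assessor would have to be unable to tell the arm from the child, the place or the assignment list. Under the table above, the place and the list each identify it. The coded datasheets in Management keep allocation from those who analyse the data, not from those who measure.

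**3. What cancels and what does not.** Let *b* be a constant offset between the arms' assessors and places, and δ the true difference in effect.

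- Post-treatment values only: expected difference = δ + *b*.
- Change from baseline, with baseline measured by the same arm-specific assessor and place: (δ + *b*) − *b* = δ.
- Baseline as a covariate with slope β: δ + (1 − β)*b*.
- Drift (offset *b*₀ at baseline, *b*₆ at week 6): the change retains *b*₆ − *b*₀.
- A proportional offset, or scoring influenced by knowledge of the arm, also remains in the change.

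**4. Size in the post-treatment-only case.** Inputs from Sample size: SD 4.974 cm², alpha 0.05, 20 per arm including 5% attrition, so 20 × 0.95 = 19 evaluable. The article gives no target difference, so the planned 20 cannot be recomputed forward. The offset *b* is an assumption, and a two-sided test is assumed.

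Standard error = 4.974 × √(2/19) = 1.61 cm². Noncentrality = (*b*/SD) × √(19/2), with 36 degrees of freedom and δ = 0:

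| Assumed offset | cm² | Noncentrality | Rejection rate |
|---|---|---|---|
| 0 | 0 | 0 | 5.0% |
| 0.2 SD | 0.99 | 0.62 | 9.2% |
| 0.3 SD | 1.49 | 0.92 | 14.7% |
| 0.4 SD | 1.99 | 1.23 | 22.4% |
| 0.5 SD | 2.49 | 1.54 | 32.3% |

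**5. Masking.** Solving backwards by the normal approximation, 19 per arm gives 80% power for 4.974 × (1.960 + 0.842) × √(2/19) = 4.52 cm². An opposing offset of 0.25 SD lowers that power to 52.8%, and one of 0.50 SD to 24.2%.

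**The case against.** **Cancellation.** The strongest reply is that an arm-specific assessor and place apply at baseline too, so a constant offset drops out of change scores and of a group-by-time test. This stands. A reader might infer that no analysis can remove the bias; that is too strong. Two conditions remain open. The article does not say that the between-group test uses change, and the cancellation needs baseline to be measured by the same assessor in the same place as follow-up.

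**Objective primary outcome.** CoP area is recorded by a force platform and computed in software from coded files, so the assessor does not score it. This also stands. Expectation bias is chiefly a matter for the tertiary measures, although instructions, stance and surface can still affect sway. The within-arm question of improvement over time is not affected by a constant between-arm offset.

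**Same assessor, same platform.** The Data collection wording on the assessor reads naturally as consistency within a child, which one assessor per arm satisfies. The platform is named by model, and units at several places could meet that. So Data collection does not flatly contradict Management on these two items. The promise of the same conditions is still hard to square with a home and a university centre.

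**Baseline timing.** A reader might infer that baseline is taken after allocation. The documents do not establish this: randomisation is stratified on a baseline ARAT score, so some baseline assessment comes first, and the figures with the flow chart and schedule are not available here.

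**Condensed article.** Brevity does not explain the blinding conflict. It lies between positive statements, not in missing detail.

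**Conclusion.** The point holds. As written, assessor and place of assessment are confounded with arm, and assessor blinding is claimed for a design that does not provide it. That conclusion is structural and needs no numerical assumption.

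The effect on the FtF–TR estimate is possible bias, of unknown size and direction. The 9% to 32% false-positive range applies only to a post-treatment-only t-test with 19 per arm and an assumed constant offset of 0.2 to 0.5 SD. The documents give no basis for choosing a value in that range. With change from baseline and a truly constant offset, the rate returns to 5%. What then remains is drift, proportional offsets and expectation bias, none of which can be sized from the documents.

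**What to change.** 1. **Cross the assessors.** Keep the two planned assessors but split each one's children across both arms by a pre-set list, with one assessor and one place per child at all visits.
2. **Name the comparison.** State in Data analysis that FtF and TR are compared on baseline-adjusted values or change from baseline. If assessor or place stays arm-specific, use change, because covariate adjustment leaves (1 − β) of a constant offset.
3. **Common set-up where feasible.** Measure both arms on the same platform and set-up at every visit. Doing so at only some visits would move a child between places and break the cancellation shown above.
4. **Align the blinding text.** If the assessors cannot be crossed, delete the assessor-blinding claim in both places under Design, describe assessment as unblinded, and state the assessor and place confounding as a limit on the FtF–TR conclusion. Even with crossed assessors, the claim is not credible while children are still measured where they are treated. Reconcile the promise of the same conditions in Data collection with Study setting and Management.

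**Cost:** no extra children or assessors. Items 1 and 3 mean travel for the assessors or the TR families. Given the distances described, and a programme meant for remote areas, this is a real burden. Items 2 and 4 are changes of text only.

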### Data collection

All measurements will be performed at the same time of the day, under the same conditions and by the same assessor at each time point. Posturographic (CoP) measures for both groups will be collected using an AMTI OR67 force platform (Watertown, MA, USA). The AMTI NetForce software (Watertown, MA, USA) will be used for the acquisition of moments and forces at 200Hz. Data will be recorded, coded, and stored on a personal computer. CoP variables will be calculated in Matlab R2012 (Mathworks Inc., Natick, MA, USA).

All primary and secondary posturographic measures will be assessed under 2 static and 4 dynamic conditions for 30 seconds each: (i) standing still with eyes open, (ii) standing still with eyes closed, voluntary sway in the mediolateral direction following a metronome set at (iii) 30Hz and (iv) 60Hz, and multidirectional sway while playing 2 different videogames that challenge (v) anterior-posterior postural control (snowboard) and (vi) medial-lateral postural control (pinguin). It is expected that all assessments, including clinical ones, will be completed within 30 minutes.

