### Sample size

Using centre-of-pressure (CoP) sway area (CoP_area_) results from earlier studies [11, 22], to achieve an 80% statistical power with an alpha level of 0.05 and considering a standard deviation of 4.974 cm^2^ (after a 6-weeks intervention), we calculated a required minimum of 20 participants in each group (FtF and TR). This sample size includes a 5% attrition, which yields a total sample size of n = 40. Sample size calculation was performed using GRANMO (Institut Municipal d’investigació Médica, Barcelona, Spain). Once the investigative work has been carried out, the sample size will be verified again, and the estimation error will be adjusted. Feasibility of this study is ensured by our previous work with similar sample size, target population, outcomes, and funding [10].

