### Interventions

This study will compare the effects of low-cost virtual reality delivered through FtF and TR modalities. The low-cost virtual reality will consist of using a Nintendo Wii balance board to play 4 exergames. In the FtF group, therapy will be provided by a physiotherapist with experience in the use of exergames for rehabilitation. In the TR modality, the intervention will be delivered by the patient’s parent or caregivers, who will be previously trained about how to deliver and assist exergames correctly and safely. In total, participants in both groups (FtF and TR) will receive 18 exergaming sessions divided in 3 sessions per week every other day (Monday, Wednesday, and Friday) over a period of 6 weeks. Each session will last for 25 minutes in which each participant will perform three series of exergames with 2-minutes rest in between games as we previously described [22]. The first two series will include Snowboard, Penguin Slide, and Super Hula Hoop. The first series will be played with arms on the side and the second one with hands on the waist to avoid the potential effect of training under one or the other strategy. The third series will be deep breathing in the Yoga game. During the first 2 weeks of training (first 6 sessions), patients will receive manual guidance and verbal instructions after which (7^th^ session onwards) only verbal instructions will be provided by the parents, caregiver, or physiotherapist.

In the Snowboard exergame patients will score by swaying (CoP displacement) in the anterior-posterior direction to swerve around flags whereas in the Penguin Slide patients will sway in the medial-lateral direction to score by catching fish while maintaining a pinguin within a continuously tilting platform. Finally, in the Hula Hoop game, patients will maintain hoops on the waist of an avatar by swaying in a (anti)clockwise circular pattern. The aim in the Yoga game will be to stand as quite as possible, first with eyes open and then with the eyes closed.

The designed low-cost virtual reality programme will be based on previous studies that have demonstrated similar interventions can effectively train postural control.^11^ For all participants in both groups (FtF and TR), adherence will be encouraged through telephone reminders. No modifications of the intervention protocols throughout the study are considered at this stage.

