### Outcomes

Differences between the effects of FtF and TR using low-cost virtual reality on postural control will be assessed using posturographic measures. In brief, posturography assesses postural control through measures of the CoP sway, of which the most commonly used are sway area (CoP_area_), and trajectories and velocities in the medial-lateral (V_ML_) and anterior-posterior (V_AP_) directions [25]. These CoP variables have been shown to be sensitive in determining changes in postural control due to training in young adults [26], patients with post-stroke hemiparesis [27], patients with Parkinson’s disease [28],^,^ and children with CP [26–28].

Primary outcome in this study will be the CoP_area_, which has been shown to be a reliable and valid measure of postural control in different clinical and nonclinical populations [22–28]. The CoP_area_ is an overall measure of the ability of the balance control system to maintain a stable upright posture, to note, higher CoP_area_ values indicate poorer balance control. The CoP_area_ has been previously and extensively used as an outcome measure of interventions aimed at improving balance control in children with atypical motor control development [29–32].

The secondary outcome measures of this study will be the standard deviation (CoP_SD_), V_ML_ and V_AP_. The CoP_SD_ is a measure of the variability of CoP displacements whereas the CoP velocity is a measure of the ability to react to changes in posture with larger values indicating poorer balance control. The latter is due to late postural adjustments lead to large CoP excursion that demand rapid corrections to maintain stability [25]. If CoP_SD_ and/or V_ML_ and V_AP_ are reduced, this will be interpreted as a beneficial effect on the intervention.

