### Data analysis

Descriptive statistics will be used to summarize the demographic and clinical characteristics in both intervention groups, and unpaired t-tests and chi-square tests will be used for comparisons. For all outcome measures, the Shapiro–Wilk and Levene tests will be used to measure the normality and homogeneity of the variance, respectively. If the assumptions of normality are met, a t-test will be employed, otherwise we will use Mann–Whitney U test to determine differences between the FtF and TR groups. Also, if the assumptions of normality are fulfilled, we will employ a repeated measures analysis of variance (RM-ANOVA), otherwise will be use Friedman’s test. Post-hoc pairwise comparisons will be used to determine the interventions effect over time for each group (FtF and TR). Cohen´s *d* will be used to report effect sizes for the CoP variables. To allow repeated measures analysis, missing data will be adjusted by 1) replacing with the non-missing average values for each variable/week, and 2) performing multiple imputations. Both methods will be used to make sure that the results were concordant. For all analyses, a *p*-value ≤0.05 will be considered statistically significant. All statistical analyses will be performed using IBM-SPSS 20.0 (SPSS Inc., Armonk, NY, USA).

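### The primary outcome, CoP area, is not tied to one of its six test conditions or one visit under a flat 0.05 threshold, and the rule that smaller is better is not justified for the four sway tasks

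*Protocol article*

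**What the plan says.** All references are to the protocol article.

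- **Outcomes** fixes the primary variable: "Primary outcome in this study will be the CoP_area" (the sway area of the centre of pressure). No condition, visit or summary over conditions is attached to it.
- **Data collection** lists six conditions: "All primary and secondary posturographic measures will be assessed under 2 static and 4 dynamic conditions for 30 seconds each". Two are quiet standing (eyes open, eyes closed). Two are "voluntary sway in the mediolateral direction following a metronome set at (iii) 30Hz and (iv) 60Hz". Two are recorded during play of the Snowboard and Penguin games.
- **Intervention timeline** gives a baseline assessment and five later ones, at weeks 2, 4, 6, 8 and 10.
- **Data analysis** plans a t-test or Mann–Whitney test between arms, RM-ANOVA or Friedman's test over time, and post-hoc pairwise comparisons within each arm. In all analyses a p-value of 0.05 or less "will be considered statistically significant". No primary comparison, hierarchy or adjustment is named.
- **Sample size** uses an SD of 4.974 cm², described as "after a 6-weeks intervention". This is the only pointer to a primary time point. The condition behind the SD is not given.
- **Outcomes** also sets the direction. For CoP area, higher "values indicate poorer balance control". If the CoP standard deviation or the velocities "are reduced, this will be interpreted as a beneficial effect on the intervention". Neither rule is limited to particular conditions.
- **Interventions** says of Snowboard that "patients will score by swaying (CoP displacement) in the anterior-posterior direction". Penguin Slide is described as side-to-side sway to catch fish while keeping the penguin on a tilting platform.

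**The concern.** Two things are left open that decide what the trial can conclude.

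First, the primary outcome is a variable, not an endpoint. With six conditions, several visits and a flat 0.05, different primary results could be reported from the same data, and nothing in the text says which one counts. The trial's message, whether of improvement, of a difference between arms or of none, could rest on whichever condition shows it.

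Second, the reading of direction comes from quiet standing, where less movement plausibly means better control. In the other four conditions movement is the task. A child who engages less with the game could show a smaller CoP area and be recorded as improved. A child who has learned to play it could move more and be recorded as worse. Snowboard and Penguin Slide are also among the games trained over the 18 sessions, so a change in task performance is to be expected there.

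**Working it through.** **The plan's own figure.** The sample size is 20 per arm, with 80% power, alpha 0.05, SD 4.974 cm² and 5% attrition. It cannot be reproduced, because no difference or margin is stated. The attrition step works: 19 / 0.95 = 20. Solving backwards for a two-sided comparison of two means with 19 evaluable per arm:

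difference = SD × (1.960 + 0.842) × √(2/n) = 4.974 × 2.802 × √(2/19) = 4.52 cm²

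This back-solved value is used below only to illustrate cost. It is an assumption, not a figure from the article.

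**Counting candidates.** Conditions: 2 + 4 = 6. Post-baseline visits: 5. There are therefore 6 candidate primary tests if visits are pooled in one model or only one visit is tested, and 6 × 5 = 30 if every condition is compared at every post-baseline visit.

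**Family-wise error.** For k independent tests at 0.05 it is 1 − 0.95^k:

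- k = 6: 1 − 0.95^6 = 0.265
- k = 30: 1 − 0.95^30 = 0.785

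The tests come from the same children, so they will be correlated. The article gives no correlation. The table shows a range of assumed common correlations, from a simulation of equally correlated normal test statistics (200,000 draws, two-sided 0.05).

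| Assumed correlation | 6 tests | 30 tests |
|---|---|---|
| 0 (formula) | 26.5% | 78.5% |
| 0.3 | 24.1% | 66.1% |
| 0.5 | 20.6% | 50.6% |
| 0.7 | 16.3% | 33.8% |
| 0.9 | 10.9% | 17.2% |

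The six-test column needs only the conditions listed in the article and one test in each. The 30-test column needs a further assumption that Data analysis does not state.

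**Keeping all six conditions as primary.** Bonferroni gives alpha = 0.05 / 6 = 0.0083. At the back-solved 4.52 cm², power with 19 evaluable per arm falls from 80% to about 56%. Restoring 80% takes 30 evaluable per arm, or 30 / 0.95 = 31.6, so 32 enrolled. Naming one condition at one visit leaves alpha at 0.05 and enrolment at 20 per arm.

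**Direction, text against text.**

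| What the rule rests on | What the condition asks |
|---|---|
| Outcomes: CoP area reflects how well a stable upright posture is kept | Quiet standing, eyes open or closed: stand still. The rule fits. |
| Discussion, on objective and clinical measures: area quantifies body oscillation in standing | Metronome conditions: sway deliberately at a set pace. No reading of area or velocity is given. |
| Outcomes: fast CoP movement reflects late corrections | Snowboard and Penguin: sway in order to score. No reading is given. |

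The construct behind the rule is stability in standing. Nothing in the article carries it over to the four tasks in which sway is instructed.

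**The case against.** The strongest reply has four parts.

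1. **Number of tests.** Data analysis attaches no visit or condition to the between-arm test, and RM-ANOVA can take the visits together. A reader might infer that 30 tests are planned, with a 79% chance of a false positive, or might count every within-arm pair of visits in every condition. The article does not say that these are all run, and correlation lowers the figure. This stands: 79% is an upper value for an unstated plan. The six conditions are untouched by it.

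2. **Direction.** A reader might infer that the rule points the wrong way in the four dynamic tasks. That is not shown. Penguin Slide also requires keeping the penguin on the platform, so excess sway could cost points. In paced side-to-side sway, a smaller area could mean less off-axis movement. This stands too: the text supports *unjustified and possibly reversed*, not *wrong*.

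3. **Scope.** This is a condensed article, and an analysis plan may settle hierarchy and adjustment. That is fair for model detail and post-hoc adjustment. But the article itself defines the primary outcome, spreads it over six conditions and fixes one threshold for all analyses. Those are statements, not omissions.

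4. **Relevance of false positives.** The between-arm hypothesis is that telerehabilitation is as effective as face-to-face delivery, and a false-positive difference works against that claim. This stands in part. The percentages measure false findings of difference or change. They do not measure the freedom to select a condition that shows no difference, which the same gap also allows.

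**Conclusion.** The point holds in a limited form. CoP area is not tied to one of six conditions or one of five post-baseline visits, and a flat 0.05 applies throughout. On the most favourable reading of visits, one test per condition, family-wise error on the primary outcome is about 26% under independence and 21% at a correlation of 0.5. It is still 11% at 0.9. If all 30 combinations were tested it would be up to 79% under independence, and 51% to 34% at correlations of 0.5 to 0.7, but the article does not state that this is done. All the correlations are assumptions.

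The direction rule is supported for the two quiet-standing conditions only. For the two metronome and two game conditions it is unjustified and may be reversed.

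A reader might also assume that the 4.974 cm² SD is a quiet-standing value. The article does not say so, and the sponsor has to confirm it.

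**What to change.** Settle the following before any data are compared by arm:

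- **Primary endpoint.** Name CoP area in one quiet-standing condition (eyes open or eyes closed, to be chosen and stated) at week 6, the time point of the SD used for the sample size.
- **SD.** Have the sponsor confirm that 4.974 cm² comes from the chosen condition. If it does not, the sample size needs a value that does.
- **Other conditions and visits.** Make them secondary, and either adjust them by Holm's method or report them as estimates with confidence intervals and no claim of significance.
- **Direction.** Limit the rule that a reduction is a benefit, for area, standard deviation and velocity, to the two quiet-standing conditions. In the metronome and game conditions, report CoP values with no pre-stated direction of benefit.

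The cost is wording only: no new data, and no loss of alpha or increase in enrolment from naming a single endpoint. The price is that fewer results can be called significant. Scoring the dynamic tasks by game score or tracking accuracy would be a larger change, since neither is a listed outcome, and this fix does not need it.
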